**Fig 1 pone.0250111.g001:**
[figure not shown]

All groups will receive an educational booklet containing information on the anatomy of the pelvis, menstrual pain, and recommendations related to dysmenorrhea. The booklet group will not receive additional treatment and will be advised not to receive treatment elsewhere during the first three months of participation in the study. This educational booklet was validated using a modified Delphi method. A group of experts discussed issues related to the practice of physiotherapy in the treatment of PD, while another group read the identified manuscripts and guidelines related to the topic. The experts had six meetings to discuss the findings and propose the booklet. Subsequently, a group of consultants, including physiotherapists who are specialists in women’s health, further analyzed, made additional contributions, and approved the booklet. Several women with DP were also consulted and approved the final version of the booklet.

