### Eligibility criteria

Participants’ inclusion criteria are as follows: women, nullipara, aged between 18 and 45 years, regular menstrual cycle, and presence of PD (pelvic or lower abdominal pain, occurring from 48 h before the onset of the menstrual period to 72 h after the first day of menstruation [2]) with pain intensity greater than or equal to four points in the Numerical Rating Scale (NRS) on the three menstrual cycles prior to their participation. The NRS considers 0 as no pain, 1–3 as mild pain, 4–7 as moderate pain, and 7–10 as severe pain [32], and only women with moderate to severe pain will be included, as more women rate their PD pain as moderate [33]. In addition, moderate to severe menstrual pain is associated with decreased quality of life [34]. Exclusion criteria for this study are as follows: pregnant, women using any kind of intrauterine device, women with skin lesions in the area where the electrodes will be placed, women with self-reported neurological or cardiac diseases, and women diagnosed with gynecological disorders (endometriosis, adenomyosis, uterine fibroids, etc.) that may be associated with secondary dysmenorrhea. The presence of any signs of skin irritation that may be associated with electrostimulation will be considered as a criterion to discontinue treatment. No concomitant care or interventions will be encouraged or forbidden during the study, but rather registered in the participant’s file.

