### Assessment of clinical outcomes

Participants who agree to participate will be assessed by a blinded assessor who will check for eligibility criteria. Subsequently, the blinded assessor will collect participants’ demographic and anthropometric data and information regarding menstrual pain medication use. Next, all eligible participants will be randomized and allocated into three groups: active TENS (aTENS), placebo TENS (pTENS), and minimum intervention group (booklet). The same blinded assessor will evaluate primary and secondary outcomes.

The primary outcome is pain intensity at baseline and three and six months after randomization. The secondary outcomes are pain intensity (only at 12 months after randomization, for the cost-utility analysis), health-related quality of life at 6 and 12 months after randomization, and pain intensity at each session before and after treatment for three months for the TENS groups. All assessment sessions are described in Table 1.

**Table 1 pone.0250111.t001:** Timeline for the schedule of enrollment, assessments, and interventions.

	Enrollment	Month 1		Month 2		Month 3		Follow-up	
		Baseline	Post	Pre	Post	Pre	Post	Month 6	Month 12
Eligibility criteria	x								
Informed consent	x								
Demographic and anthropometric data	x								

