### Economic assessment

Economic assessment will be done from a healthcare and societal perspective. Incremental cost per quality-adjusted life-years (QALYs) of the interventions will be used for cost-effectiveness and cost-utility analysis, considering both healthcare and societal perspectives, measuring direct and indirect costs. The Numerical Rating Scale will be used for cost-effectiveness analysis, and the SF-6D questionnaire will be used for cost-utility analysis. Cost data will be collected by a cost questionnaire that will be sent to the participant via WhatsApp® at 3, 6, and 12 months after baseline. All costs related to menstrual pain will be considered, either direct (costs of the participant to health systems, public and private, and out-of-pocket expenses) and indirect (unpaid productivity loss), which include intervention, healthcare, informal care, and unpaid productivity costs. Intervention costs will be estimated based on the physical therapy board fee schedule (according to the Federal Physical Therapy and Occupational Therapy Council, USD 11.32 per TENS application– 2020 fee which is equivalent to R$ 64.63 rate converted to US dollars using the 04/02/2021 conversation rate [41]). Healthcare costs, including primary and secondary healthcare costs, will be priced using Brazilian standard costs. Both prescribed and over-the-counter medication use will be priced using the prices of the Brazilian pharmaceutical websites and medical services fee schedule.

A Portuguese/Brazil validated version [42] of the Stanford Presenteeism Scale [43] will be used to measure presenteeism from paid work, and the estimated price of productivity losses per sickness absence day for women, according to the average wage in the state of São Paulo per hour.

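### The protocol states a neutral rule on concomitant care, but advises only the booklet arm against other treatment for three months, which can bias the TENS-versus-booklet comparisons

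*Protocol article*

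**What the plan says.** Two current statements in the protocol article govern treatment outside the trial.

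- **Eligibility criteria**, for the whole trial: "No concomitant care or interventions will be encouraged or forbidden during the study". Such care is only to be recorded in the participant's file.
- **Interventions**, for one arm: the booklet group gets nothing further from the trial and "will be advised not to receive treatment elsewhere during the first three months of participation in the study".

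The Interventions section first describes what is common to the three arms: "All groups will receive an educational booklet containing information on the anatomy of the pelvis, menstrual pain, and recommendations related to dysmenorrhea". The advice comes after that and is attached to the booklet group alone.

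Three other parts of the article bear on the consequences.

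- **Assessment of clinical outcomes** sets the primary time points: "The primary outcome is pain intensity at baseline and three and six months after randomization".
- **Economic assessment** sets the cost collection, with times counted from baseline: "Cost data will be collected by a cost questionnaire that will be sent to the participant via WhatsApp® at 3, 6, and 12 months after". The scope is wide: "All costs related to menstrual pain will be considered, either direct" or indirect, with health-system and out-of-pocket spending counted as direct.
- **Statistical analysis** says that possible confounders, with use of pain medication as an example, will be recorded and used in the analysis. It does not say how.

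**The concern.** Advising participants against other treatment is not neutral, so site staff cannot follow both statements in the booklet arm. No other part of the article reconciles them.

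If staff follow the Interventions section, the booklet arm differs from the TENS arms in two ways: it receives no TENS, and it has been told to stay away from other treatment. The second difference is in force over the months that lead up to the first post-baseline primary assessment and the first cost questionnaire. The month-3 contrast between active TENS and booklet would then combine the effect of TENS with the effect of discouraging other care in the comparator. The Abstract names that contrast in the study hypothesis, beside active versus placebo TENS, and the booklet arm is the only comparator without a device.

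Other treatment is likely to be in play. Women enter with pain of at least 4 on the NRS, and the Introduction lists analgesics, anti-inflammatory drugs and hormonal contraceptives among the most used interventions.

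**Working it through.** The article gives no figure that quantifies this point, so there is nothing to reproduce. The check sets the passages side by side and then shows, on assumed values, how large a shift could be.

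**1. Which arm is told what**

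| Arm | Eligibility criteria | Interventions |
|---|---|---|
| Active TENS | neutral, recorded | no advice stated |
| Placebo TENS | neutral, recorded | no advice stated |
| Booklet | neutral, recorded | advised against other treatment, months 0 to 3 |

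The statements conflict only in the booklet row. The two TENS rows are identical, so active versus placebo TENS is untouched.

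**2. Which results fall in the window**

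- Pain at month 3 (primary): at the end of the advice period, directly exposed.
- Pain at month 6 (primary) and month 12 (secondary): after the advice has lapsed, less exposed.
- Costs: the month-3 questionnaire presumably covers months 0 to 3 (the recall period is not stated). Those costs also enter any 12-month total.

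**3. Pain: direction and possible size**

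Shift in the TENS-versus-booklet mean difference = (reduction in uptake of other treatment in the booklet arm caused by the advice) × (mean NRS reduction from that treatment).

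Both inputs are assumptions; the article gives neither. Shift in NRS points, in favour of TENS:

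| Uptake lower by | effect 0.5 | effect 1 | effect 2 |
|---|---|---|---|
| 10 points | 0.05 | 0.10 | 0.20 |
| 20 points | 0.10 | 0.20 | 0.40 |
| 30 points | 0.15 | 0.30 | 0.60 |
| 50 points | 0.25 | 0.50 | 1.00 |

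The range is 0.10 × 0.5 = 0.05 to 0.50 × 2 = 1.0 points.

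**4. Costs and the ratio**

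Let ΔC and ΔE be the cost and effect differences, TENS minus booklet, with ΔE counted as benefit. If the advice lowers booklet-arm costs by c and raises its pain by b, the estimates become ΔC + c and ΔE + b. With ΔE and b positive, the ratio (ΔC + c)/(ΔE + b) exceeds ΔC/ΔE only when c/b exceeds ΔC/ΔE. The documents give none of these quantities, so the net direction is open. From the societal perspective, less treated pain in the booklet arm could also raise its productivity losses, which would offset c in part or whole.

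**5. Whether the planned analysis repairs it**

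- If the medication variable is the baseline value, it says nothing about treatment forgone later because of the advice.
- If it is use after randomization, it is itself a consequence of the arm-specific advice and also depends on how much pain the woman has. Adjusting for it conditions on something that allocation changed, and does not in general recover the comparison under equal instructions.
- Intention-to-treat does not help, because the advice is part of what the booklet arm is assigned.

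**The case against.** Several points on the other side are sound.

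- **It is advice, not a prohibition.** Adherence is unknown, and at the low end of the assumed range the shift is negligible. This stands: the advice can bias the comparison, and nothing shows that it will.
- **Its scope is undefined.** It may refer to care from other providers and leave self-medication alone. The article plans to collect pain-medication use, so some use is expected. This stands too. An effect on medication costs depends on one reading of an unclear phrase, and the lack of definition is itself something to resolve.
- **A minimum-intervention comparator may be intended.** The article uses that description for the booklet arm and does not say that the target is TENS added to otherwise equal care. An arm-specific instruction could therefore be deliberate. That would justify the Interventions wording, but the whole-study statement under Eligibility criteria would then be wrong.

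A reader might infer more than the documents support. One inference is that the trial's pain and cost comparisons are biased as a whole. They are not: neither TENS arm is given the advice, and month-6 pain lies outside the window. Another is that the shift could absorb most of the planned effect. Converting the f of 0.20 in Sample size calculation into a largest pairwise difference gives 0.20 × 3/√2 = 0.42 SD or 0.20 × √6 = 0.49 SD, depending on the pattern of the three means. However, that f belongs to a repeated-measures analysis whose tested effect is not named, and the article gives no SD for the NRS. Setting an assumed shift against those figures would give a false impression of precision.

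**Conclusion.** The contradiction is real and rests on the text alone. If the advice in the Interventions section is given as written, it can bias the comparisons of either TENS arm with the booklet arm. Month-3 pain would tend to be shifted in favour of TENS. Health-care costs in months 0 to 3 would tend to be lower in the booklet arm, which counts against TENS on incremental cost. No net direction for cost-effectiveness can be claimed.

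The size is unknown. The range of 0.05 to 1.0 NRS points is an illustration that depends wholly on the assumed uptake difference (10 to 50 percentage points) and effect of other treatment (0.5 to 2 points). The planned use of medication data in the model does not remove the problem.

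**What to change.** 1. Reconcile Eligibility criteria and Interventions so that the instruction on concomitant treatment is stated once, says which treatments it covers (including whether self-medication counts) and over what period, and makes clear how it applies to each arm. Which rule to adopt is for the investigators.
2. If the instruction still differs between arms after reconciliation, say so where the comparisons are defined, and interpret the TENS-versus-booklet contrasts, for pain and for costs, as including that difference.
3. Report co-treatment by arm at each assessment, and do not present adjustment for use after randomization as a correction.

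The cost is a wording change in the protocol and the participant instructions. Concomitant care is already to be recorded, so the reporting needs a table rather than new data collection. The change protects the data only for participants who have not yet passed through the three-month window, so it is best made before or early in enrolment.

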## Discussion

### Potential impact and significance of the study

This is the first study that proposes a health economic evaluation alongside assessing the benefits of using TENS to treat PD symptoms. As such, the results of the present study may contribute to the PD research agenda. Although TENS is used to treat PD symptoms [16] and has been shown to reduce pain with minimum adverse effects [15], the studies are considered of low to moderate quality [16] and lack information on parameters and clinical considerations [15], which makes it difficult to compare results and to establish the best parameters of electrical stimulation. Understanding whether TENS is really cost-effective for PD pain treatment opens possibilities to include this resource as a recommendation, and with that, call the attention of both professionals and women to the fact that PD can be treated. Improving PD symptoms may mean, at last, that the economic impact of this disease may be reduced by either decreasing presenteeism or the use of medications and health care services due to PD pain.

### Contribution to professionals and patients

It is not very common for women to seek help due to PD pain, usually because PD is not recognized as a legitimate health issue, not only by women, but also by health care providers and society [52]. The present study can attract attention to the issue and, as such, allow health care providers and women to start looking at PD as a health issue that has nonpharmacological interventions as a treatment resource. If TENS is proven cost-effective for the treatment of PD pain, health care managers may recommend the use of electrical stimulation for this common symptom, and some professionals, such as physical therapists and nurses, can start assisting women during this period, practicing evidence-based care. Women will have more information on the possible nonpharmacological interventions to treat their pain, with more resources at their disposal, and have their quality of life improved. This may lead to an increase in the seek for health care related to the menstrual period, but also to a decrease in the number of working hours or days lost due to PD symptoms.

### Strengths and weaknesses of the study

The strengths of the present study are that this is the first prospective study that aimed to assess the cost-effectiveness of TENS for PD pain. This is a randomized controlled clinical trial in which researchers, participants, and physical therapists are blinded to participants’ allocation and to the aim of the present study. The sample size was appropriately calculated to provide enough power to detect differences in the primary outcome. The statistical plan analysis includes the intention-to-treat analysis and intends to assess all women who discontinue intervention. One limitation of the present study is that even though participants allocated to the TENS groups (both active and placebo) will be blinded to their allocation, it is not possible to blind participants in the Booklet group.

### Future research

The present study opens new possibilities for new investigations on nonpharmacological interventions for PD. Future studies could include combinations of TENS and more long-term interventions such as exercises, yoga, and manual therapy, and analyze the cost-effectiveness of the combination of these techniques.
